### 2.3 Definitions for Primary and Secondary Endpoint Calculations

[Supplementary Table 2](#)

|               | Prognostic reference standard |           |            |           |
|---------------|-------------------------------|-----------|------------|-----------|
|               | Positive                      | Negative  | Ungradable | Total     |
| IDx-DR Result |                               |           |            |           |
| Positive      | PP                     | PN | PU  | DP |
| Negative      | NP                     | NN | NU  | DN |
| Ungradable    | UP                     | UN | UU  | DU |
| Total         | TP                     | TN | TU  | N  |

[figure not shown]

|                     |               |        |             |
|---------------------|---------------|--------|-------------|
| CTMF-SA-DXSDR006-03 | SAP_2.1_clean | Rev. A | Pg. 6 of 16 |
|---------------------|---------------|--------|-------------|

*Endpoints:*

$$\text{Sensitivity} = \frac{PP}{PP+NP}$$

$$\text{Specificity} = \frac{NN}{PN+NN}$$

$$\text{Positive Predictive Value} = \frac{PP}{PP+PN}$$

$$\text{Negative Predictive Value} = \frac{NN}{NP+NN}$$

$$\text{Diagnosibility} = \frac{PP+PN+NP+NN}{TP+TN}$$

*Endpoints considering ungradable eyes:*

$$\text{Sensitivity}_{+u} = \frac{PP}{PP+NP+UP}$$

$$\text{Specificity}_{+u} = \frac{NN}{PN+NN+UN}$$

$$\text{PPV}_{+u} = \frac{PP}{PP+PN+PU}$$

$$\text{NPV}_{+u} = \frac{NN}{NP+NN+NU}$$

#### **2.4 Precision Substudy Primary Objective:**

The primary objective of the precision substudy is to evaluate the repeatability and reproducibility of IDx-DR with the RV700.

#### **Precision Substudy Endpoints:**

For the Precision Substudy, the following will be analyzed:

1. Eye-level DDx algorithm mixed model estimates of the operator, camera, sequence, dilation, and FPRC effects
2. Average positive agreement (APA) in intra- and inter- configurations of RV700 cameras/operators
3. Average negative agreement (ANA) in intra- and inter- configurations of RV700 cameras/operators
4. Average ungradable agreement (AUA) in intra- and inter- configurations of RV700 cameras/operators
5. Overall agreement
6. Subject-level DDx algorithm mixed model estimates of the operator, camera, sequence, dilation, and FPRC effects.

### **3. Design and methods**

**3.1 Cohort:** This is a Diagnostic Performance Study, where a minimum of 200 eyes with mtmDR and at least 140 eyes without mtmDR will be enrolled at primary care sites. The study population is expected to mirror the spectrum of disease severity encountered in primary care settings, from no DR to proliferative DR (PDR), with a target sample size of at least 200 eyes (~20% of subject sample size) with more than mild DR (mtmDR+), which includes ETDRS levels 37-85, and/or clinically significant as well as center-involved macular edema as subgroup analyses. The study population is also expected to mirror the racial and ethnic distribution of the US diabetes population. Within this cohort, at least 20 eyes are expected to have vision

[figure not shown]

|                     |               |        |             |
|---------------------|---------------|--------|-------------|
| CTMF-SA-DXSDR006-03 | SAP_2.1_clean | Rev. A | Pg. 7 of 16 |
|---------------------|---------------|--------|-------------|

threatening DR (vtDR), defined as ETDRS level 53-85 and/or clinically significant as well as center-involved macular edema; overweighted sampling will be used to meet this vtDR goal.

The overweight sampling will be performed with a sample of 1,000 random draws to expand the number of ETDRS eyes with the level of at least 53 from a minimum of 20 eyes to represent 20% mtmDR(+). The minimum of 20 eyes must be reading center gradable and sufficient, Specificity calculations will rely on those eyes with ETDRS level less than 37. The sampling will be conducted before any analyses are performed.

**3.2 Precision Substudy sample:** Select subjects will be invited for the Precision Substudy based on the PRS grading of their Diagnostic Performance Study images. Eighteen (18) of the Precision substudy subjects will have received a grade of mtmDR(+) in at least one eye, and eighteen (18) will have received a grade of mtmDR(-) in both eyes. Subjects will be fully dilated and then undergo nine IDx-DR exams. The substudy will test three RV700 cameras, three operators, and three replicates using a Latin Square design. The camera, operator, and replicate combinations across subjects are specified below:

|         |                                     |
|---------|-------------------------------------|
| Exam A: | RV700 A + Operator #1 (Replicate 1) |
| Exam B: | RV700 A + Operator #2 (Replicate 1) |
| Exam C: | RV700 A + Operator #2 (Replicate 2) |
| Exam D: | RV700 B + Operator #2 (Replicate 1) |
| Exam E: | RV700 B + Operator #3 (Replicate 1) |
| Exam F: | RV700 B + Operator #3 (Replicate 2) |
| Exam G: | RV700 C + Operator #1 (Replicate 1) |
| Exam H: | RV700 C + Operator #1 (Replicate 2) |
| Exam I: | RV700 C + Operator #3 (Replicate 1) |

The Latin Squares design follows where the X represents an observation and R represents a replicate in order to estimate camera effect, operator effect, and reproducibility:

|          | Operator 1 | Operator 2 | Operator 3 |
|----------|------------|------------|------------|
| Camera A | X          | X, R       | -          |
| Camera B | -          | X          | X, R       |
| Camera C | X, R       | -          | X          |

Operators will reposition subjects between each imaging replicate. The order of the data collection will be recorded in the case report form.

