**5.2 Precision Substudy:** The repeatability and reproducibility substudy will be performed including three cameras and three operators (see Section 3.2). A Latin Squares design (Supplementary Table 6) will be used with mixed effects models used to analyze the DDx algorithm outcome data on a log-scale with operator, camera, sequence, dilation, and FPRC as covariates. Separate analyses will be performed at the subject-level and at the eye-level. Each of 36 subjects, 50% positive for mtmDR in at least one eye, will have a total of 9 results on each eye (see protocol Section 9.4.1). Repeatability will be assessed within the three replicates from pre-specified camera-operator pairs, and reproducibility will be assessed from comparing results across the six camera-operator combinations. There will be 3 replicates on all 36 subjects (72 eyes) for 216 gradings for the replicate analyses and 6 measures on all 36 subjects (72 eyes) for 432 gradings for the reproducibility analysis.

[figure not shown]

|                     |               |        |              |
|---------------------|---------------|--------|--------------|
| CTMF-SA-DXSDR006-03 | SAP_2.1_clean | Rev. A | Pg. 13 of 16 |
|---------------------|---------------|--------|--------------|

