## **4.2. Scientific Rationale for Study Design**

In order to add an additional fundus camera model to IDx-DR's indications for use, a camera qualification study must be conducted that shows IDx-DR paired with the new camera (RV700) is substantially equivalent to the predicate device, the IDx-DR paired with the NW400. The proposed study is a multicenter, preregistered prospective study design that will measure the sensitivity and specificity of IDx-DR with the RV700. A Level I prognostic reference standard will be determined by retinal experts at a qualified reading center, who will each independently grade the images according to the Early Treatment of Diabetic Retinopathy Study severity scale and the Diabetic Retinopathy Clinical Research Network (DRCR) macular edema severity scale [12] from 4W color, stereoscopic fundus and macular OCT images, and also a Level II reference standard by the same reading centers, reading the RV700 images.

The subject population is intended to mirror the DR/DME disease spectrum encountered in primary care settings.[10] Primary care sites will be used as enrollment sites for an intent to screen, study design and mimic real-world use at a non-specialist clinic setting.

In order to also study other variables that may impact the use of IDx-DR with the RV700, such as intra-operator and intra-camera variability, a separate substudy focused on precision will be conducted within this study. The Precision Substudy will invite a subset of subjects enrolled in the main study to undergo a series of fundus imaging sessions with various RV700 units and operators.

While subjects in the main Diagnostic Performance Study will only be dilated as needed, all subjects entering the Precision Substudy will undergo dilation. All instances of dilation will use Tropicamide 1%. Repeated imaging causes subject pupil constriction, and therefore, undilated study subjects would require substantial time between imaging sessions for pupil constriction recovery (previously found to be 15 minutes in the IDx-DR pivotal precision substudy). The minimum amount of time required to complete the nine exams within the Precision Substudy protocol with a dilate “as needed” contingency and adequate pupil response recovery would be approximately half a clinic day, making subject enrollment in the afternoon difficult. Therefore, dilation of all subjects prior to the Precision Substudy imaging has been included in the study design.

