subject identifier will be composed of two parts: a two-digit site identifier and a three-digit unique subject number separated by a delimiter. For example: the 3rd trial site enrolling their 12th subject will have a subject identifier of “03-012”. The Precision Substudy will make use of these subject identifiers and append a one-character IDx-DR Exam ID separated by a delimiter, corresponding to the specific camera-operator-replicate configuration (see table in Section 1.3.4). For example, if subject 03-012 is invited into the Precision Substudy, assigned to Imaging Sequence 1, then that exam would be identified as “03-012-1”.

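### No scheme is defined for the order of the nine Precision Substudy exams, so whether camera and sequence effects can be separated depends on how sites choose to run them

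*Combined protocol and SAP*

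**What the plan says.** **Layout.** SAP 3.2 and protocol 9.4 list nine exams, A to I, grouped by camera: camera A with operators 1, 2, 2; camera B with 2, 3, 3; camera C with 1, 1, 3. The stated purpose of the square is "in order to estimate camera effect, operator effect, and reproducibility". Its rows are cameras and its columns are operators.

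**Order.** Both sections give one sentence on it: "The order of the data collection will be recorded in the case report form".

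**Analysis.** SAP 5.2 fits mixed models to the log-scale algorithm score with "operator, camera, sequence, dilation, and FPRC as covariates". SAP 2.4 makes the estimates an endpoint: "Eye-level DDx algorithm mixed model estimates of the operator, camera, sequence, dilation, and FPRC effects". A subject-level version is listed too.

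**Traces of a sequence scheme.**
- Protocol 6.4 gives the example of a subject "assigned to Imaging Sequence 1, then that exam would be identified as" a number ending in 1. Protocol 1.3.5 instead ends the identifier with the exam letter.
- The protocol contents list a section 1.3.2 on imaging sequences with a broken bookmark. In the body, 1.3.2 is the exam procedure.
- Protocol 9.4.1 has Imaging Sequence in its title but gives no order across subjects. It shows one operator per camera with three replicates, which is not the nine-exam layout.

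The substudy schema and exam-procedure figures are not shown in the text available.

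**The concern.** This is a nine-period within-subject comparison. In such a design, anything that changes over the visit is mixed with whatever was used early or late, unless order varies independently of camera and operator. Recording the order allows adjustment only if the order does vary in that way, and nothing in the readable text requires it.

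Time trends are plausible. Protocol 7.6 allows for sessions of more than three hours with operators new to retinal imaging, and protocol 4.2 notes that "Repeated imaging causes subject pupil constriction". If the cameras were always used in the same order, a worse result on the last one could come from the camera or from the passage of time. The planned sequence estimate would be weak or unavailable.

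**Working it through.** **Plan's own counts.** "Each of 36 subjects, 50% positive for mtmDR in at least one eye, will have a total of 9 results on each eye". So 36 × 2 = 72 eyes; 72 × 3 = 216 replicate gradings and 72 × 6 = 432 reproducibility gradings, as SAP 5.2 states; 216 + 432 = 648 = 72 × 9. These figures reproduce. The plan states no power, margin or effect size for the substudy.

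**Check.** I examined the fixed-effects design matrix with 36 subject effects, 2 camera, 2 operator and, for categorical position, 8 position columns: 36 + 2 + 2 + 8 = 48. One result per exam per subject is used, and variances are in units of the residual variance.

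**Case 1: everyone imaged A to I (an assumption).** Mean positions are 2, 5 and 8 for cameras A, B and C.

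- *Categorical position.* Position determines both camera and operator, so those 4 columns add nothing. Rank = 36 + 8 = 44 of 48, and C-minus-A is not estimable.
- *No position term.* Regress position 1 to 9 on camera and operator. The coefficients are B-minus-A = 2, C-minus-A = 6, operator 2-minus-1 = 1, operator 3-minus-1 = 2, intercept 4/3. A drift of d per exam therefore biases C-minus-A by 6d and B-minus-A by 2d.
- *Linear position.* The residuals of that regression are −1/3 for six exams and +2/3 for C, F and H. Their sum of squares per subject is 6 × 1/9 + 3 × 4/9 = 2, so 72 over 36 subjects. Without position, Var(C−A) = 1/36 = 0.0278. With it, Var(C−A) = 0.0278 + 6²/72 = 0.5278, and 0.5278 / 0.0278 = 19.
- *Linear position plus replicate.* C, F and H are exactly the second replicates. Adding the replicate effect named in protocol 8.1 therefore removes estimability again (rank 41 of 42).

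**Case 2: cameras always A, B, C, order varied only within camera.** The two camera columns remain determined by position: rank 46 of 48, C-minus-A not estimable with categorical position.

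**Case 3: order varies across cameras.**
- One simulated random order per subject: rank 48 of 48, Var(C−A) = 0.0285, about 2.5% above 0.0278.
- 27 subjects forward and 9 reversed: C-minus-A estimable, variance 0.046 with categorical position.

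**Case 4: three camera blocks rotated over their 6 orders, 6 subjects each, listed order within block.**
- Categorical position: rank 48 of 48. Var(C−A) = 0.0278 (ratio 1.0); Var(B−A) = 0.0417 (0.0417 / 0.0278 = 1.5); operator 3-minus-1 = 0.0833 (ratio 3.0).
- Linear position: B-minus-A 0.0283 and operator 3-minus-1 0.0298, both close to 0.0278.
- No position term: C-minus-A has no linear-drift bias, but B-minus-A keeps −d, operator 2-minus-1 keeps d and operator 3-minus-1 keeps 2d.

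**The case against.** **The A-to-I order is assumed.** No section prescribes it; the letters are exam codes. A reader might infer that camera and sequence effects cannot be separated at all. The documents do not support that: Case 3 shows separation as soon as order varies across cameras. The categorical coding is also an assumption, since SAP 5.2 only names sequence as a covariate. This stands, and it makes the point conditional.

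**An assignment may exist.** Protocol 6.4 speaks of one and two figures are missing. The supportable statement is that the readable text defines no scheme, not that order is never assigned.

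**Pupil drift is already addressed.** The remark on constriction in protocol 4.2 explains why all substudy subjects are dilated. Protocol 7.6 adds gaps of at least five minutes and re-dilation, and dilation is a covariate. This largely answers the pupil argument, but not other within-session trends.

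**Operator learning runs mainly across subjects.** A reader might infer that it falls wholly on the later cameras. Suppose subjects are imaged one after another with linear learning per exam. C-minus-A then carries 6 of 323 steps (36 × 9 − 1), or 1.9%, in one series, and 6 of 161 (18 × 9 − 1), or 3.7%, with 18 subjects at each of two sites.

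**Agreement statistics remain computable.** Four of the six substudy endpoints are agreement measures that do not require camera and position to be separated. A reader might infer that the reproducibility objective cannot be met; that goes too far. These tables are, however, unadjusted for position. Under A-to-I order the replicate pairs (B-C, E-F, G-H) are one exam apart and between-camera pairs average four apart. Drift would tend to lower inter-configuration agreement more, and could be read as camera or operator variability. That direction is conservative.

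**Conclusion.** The point holds as a conditional design weakness. The readable text defines no exam order, the square does not balance position, and both camera and sequence effects are promised estimates. Whether those estimates can be had depends on what sites do.

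The size runs from almost nothing (variance about 2.5% higher under random orders) to complete loss of C-minus-A under a uniform A-to-I order with categorical position. Under that order it is a 19-fold variance with linear position, or a bias of 6d with no position term. The drift d is unknown; the documents give no value.

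The figures assume complete data, independent residuals of equal variance, and the same three cameras and operators for all 36 subjects. Protocol 4.1 mentions two sites, so the last assumption should be confirmed. The effect is confined to the substudy; the primary sensitivity and specificity tests are untouched.

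**What to change.** 1. Pre-assign the order. Rotate the three camera blocks over their 6 possible orders, 6 subjects per order (3 mtmDR(+) and 3 mtmDR(−)), allocated at random. Keep each replicate pair together within its block.
2. Keep exam position in the mixed model and state whether it is linear or categorical. Rotation alone leaves some drift in B-minus-A and the operator contrasts.
3. Record the actual order as well as the assigned one.
4. Reconcile protocol 6.4, the contents entry for 1.3.2 and section 9.4.1 with the nine-exam list.

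Block rotation is preferable here to an 18-sequence Williams design over all nine exams. That design also separates the effects, but it puts replicate pairs next to each other in only 4 of 18 sequences and runs replicate 2 before replicate 1 in 9 of 18, so repeatability would absorb time and camera changes.

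Cost: a sequence table, a site instruction and some loss of scheduling freedom, with no extra subjects, exams, cameras or operators. With categorical position, B-minus-A has about 1.5 times the variance it has without a position term, and operator 3-minus-1 about 3 times if the listed order is kept within blocks. C-minus-A is unchanged. A linear term costs much less but assumes a straight-line trend.

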#### 4. Sample size calculations

**Assumptions:** In this study, a minimum of 200 eyes with mtmDR and at least 140 eyes without mtmDR will be enrolled in the main diagnostic performance study; enrollment will be continued until a minimum of 20 vtDR eyes are confirmed to be sufficient and gradable. The device performance will be evaluated per eye. The primary endpoints will be the sensitivity and specificity of IDx-DR paired with the RV700 in detecting mtmDR based on eye-level results when compared to a PRS by three retinal experts.

[figure not shown]

|                     |               |        |             |
|---------------------|---------------|--------|-------------|
| CTMF-SA-DXSDR006-03 | SAP_2.1_clean | Rev. A | Pg. 8 of 16 |
|---------------------|---------------|--------|-------------|

The predicate device, IDx-DR with the NW400, pivotal trial pre-specified null hypotheses for sensitivity and specificity of 75% and 77.5%, respectively; these represent pre-defined non-inferiority margins. The alternative hypotheses were 85.0% for sensitivity and 82.5% for specificity in support of a non-inferiority design. These lower thresholds for performance will be ruled out with one-sided 97.5% confidence bounds.

As this study is intended to support an extension of the IDx-DR labeling to validate a new camera for use with IDx-DR, the performance is expected to be substantially equivalent to the predicate device at the subject-level.

This study will validate the use of a new camera with the same diagnostic algorithm as currently on the market. The proposed sample size maintains a one-sided 97.5% confidence interval that exceeds the predicate device pivotal trial null hypotheses, i.e., a lower confidence limit  $> 75\%$  for sensitivity and  $> 77.5\%$  for specificity which reflects a 5% non-inferiority offset for sensitivity and a 2.5% non-inferiority offset for specificity (see **Supplementary Table 3** columns 1-4). These hypothesis tests were designed specifically to reflect clinically meaningful eye-level outcomes; substantial equivalence is interpreted as non-inferiority

(**Supplementary Table 3** columns 1-4).

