| 1. To demonstrate the substantial equivalence of IDx-DR using the RV700 to the predicate device (IDx-DR using the NW400) in detecting ETDRS level 35 or higher and/or DME                                                                                                                                                                                                                                                                                                                        | 1. Sensitivity and specificity of IDx-DR using RV700 based on eye-level results against a Level I Prognostic Reference Standard (PRS)
2. Eye-level sensitivity calculated using weighted sampling so that ETDRS level 53 or higher represents 20% of the mtmDR(+) sample                                                                                                                                                                                                                                                                                                                                                                                                                                                                                                                                                                                                                                                                                                                                                                                                                                                                  |

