| $d_1 = 0.085$ is the difference at which power is calculated. $d_1 = p_1 - p_0$ and is the hypothesized sensitivity value above the non-inferiority threshold                         | $d_1 = 0.096$ is the difference at which power is calculated. $d_1 = p_1 - p_0$ and is the hypothesized specificity value above the non-inferiority threshold                         |        |             |
| n=200 mtmDR(+) eyes                                                                                                                                                                   | n=140 mtmDR(-) eyes                                                                                                                                                                   |        |             |
| Reject $H_0$ for at least 163/200 true positive eyes, or at least 81.2% sensitivity.
Establish superiority for at least 172/200 true positive eyes, or at least 85.7% sensitivity. | Reject $H_0$ for at least 119/140 true negative eyes, or at least 84.6% specificity.
Establish superiority for at least 122/140 true-negative eyes, or at least 86.7% specificity. |        |             |

The mtmDR(+) and mtmDR(-) sample size depends on the WRC findings so the study will enroll to a target of 564 eyes (282 subjects maximum) to ensure sufficient numbers for the sensitivity and specificity analyses. In addition, in order to achieve 200 mtmDR(+) eyes, we anticipate >450 mtmDR(-) eyes will be accrued based on the historical enrollment ratio (1:4). Thus, the specificity power will be increased and the threshold to establish non-inferiority and superiority will be reduced. Similarly, in the event that >200 mtmDR(+) eyes are determined, all eyes will be included. Thus, the plan is to include all recruited subjects in the final analyses in support of the intent to diagnose analysis principle.

Additionally, weighted sampling will be performed by sampling with replacement among eyes with ETDRS levels at least 53 for computing sensitivity, PPV, and NPV in settings with higher prevalence of severe disease. The overweight sampling is expected to achieve similar sensitivity due to the samples being drawn at random from the gradable and sufficient eyes with ETDRS greater than 53. This analysis is being done following discussion with FDA to assess PPV and NPV outcomes in populations with different vision threatening incidence.

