#### 7.4. Enrichment Cohort

In order to assure an adequate range of DR conditions in the study population sample, and avoid spectrum bias, for sensitivity and specificity analysis, the primary care study population may be enriched following the pre-specified formal evaluations outlined in the Data Transfer Plan, to ensure a sufficient range of diabetic retinopathy severity within cases. The enrichment cohort will be targeted using HbA1c levels, if needed, and will draw from the same pool of intent to screen subjects as the non-enriched subjects. To avoid excessive enrollment in any one stratum, the totals will be monitored weekly. Participant enrichment will be targeted based on elevated HbA1c, factors which have been shown to be correlated with higher rates of mtmDR among patients with diabetes. No cap will be placed on enriched participants since such participants will be prospectively recruited. The goal will be to recruit enough subjects to satisfy each stratum. If enrollment patterns are not on track with the study's target population after periodic reviews, enrollment at all sites will be adjusted monthly by modifying the HbA1c. Adjustments from this level may be instituted after a periodic review of the stratum enrollments reflecting the number of participants with diabetic retinopathy or diabetic macular edema. Study sites will be notified by the CRO if there is to be a change in the HbA1c thresholds. Once the total number of cases has been projected in alignment with statistical power requirements, then the final adjustments to participant enrollment criteria will be performed.

Monitoring of strata will be performed by the study statistician (without access to IDx-DR results); only available HbA1c, along with FPRC categorization into mtmDR and vtDR, will be visible for each subject included to date. The study statistician will notify the CRO whether updated HbA1c thresholds are needed. Again, once the strata targets for mtmDR and no/mild DR can be projected, the HbA1c thresholds will be locked.

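### The enrolment condition counts 20 vtDR eyes, some of which may qualify on macular edema alone, so it does not guarantee the 20 eyes at ETDRS 53 or higher that the SAP's weighted primary endpoint starts from

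*Combined protocol and SAP*

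**What the plan says.** **Enrolment (SAP Section 4).** The minima are "a minimum of 200 eyes with mtmDR and at least 140 eyes without mtmDR will be enrolled in the main diagnostic performance study", and in addition "enrollment will be continued until a minimum of 20 vtDR eyes are confirmed to be sufficient and gradable". The same section sets a maximum of 282 subjects (564 eyes).

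**Meaning of vtDR (SAP Section 3.1).** It is "defined as ETDRS level 53-85 and/or clinically significant as well as center-involved macular edema".

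**Second primary endpoint (SAP Section 2).** "Eye-level sensitivity calculated using weighted sampling so that ETDRS level 53 or higher represents 20% of the mtmDR(+) sample".

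**Base for the weighting (SAP Section 3.1).** The resampling is to "expand the number of ETDRS eyes with the level of at least 53 from a minimum of 20 eyes to represent 20% mtmDR", and "The minimum of 20 eyes must be reading center gradable and sufficient". SAP Section 4 confirms the pool: "weighted sampling will be performed by sampling with replacement among eyes with ETDRS levels at least 53". Macular edema does not enter it.

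**Monitoring (Protocol 7.4).** For the statistician who steers enrichment, "only available HbA1c, along with FPRC categorization into mtmDR and vtDR, will be visible for each subject included to date".

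**Protocol on vtDR (Sections 4.1, 7.3 and 9.1).** The protocol expects at least 40 vtDR eyes. Sections 4.1 and 9.1 define vtDR as ETDRS 50-85 and/or macular edema.

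**The concern.** Two severe-disease groups share the number 20. The enrolment condition counts vtDR eyes, and the and/or in the definition admits an edema eye below level 53. The weighted endpoint can use only eyes at level 53 or higher. The second group is a subset of the first, so reaching 20 in the first does not establish 20 in the second.

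The monitoring described in Protocol 7.4 would not reveal a gap, because it shows vtDR status but not whether an eye is at level 53 or higher. The plan also does not say what happens if 282 subjects are enrolled before either count of 20 is reached.

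At stake is how much information lies behind the 20% weight in the weighted sensitivity, and behind the weighted PPV and NPV drawn from the same eyes. With fewer than 20 distinct eyes, each is drawn more often and counts for more. The estimate still looks like one built on the SAP's stated base.

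**Working it through.** **1. The plan's own figure.** The documents give no power or sample size for the weighted endpoint. Their figure is for the unweighted sensitivity test: 200 eyes, 75% against 83.5%, one-sided 0.025, 80% power, rejection at 163/200 or more. An exact binomial calculation gives the same cut-off of 163 (actual alpha 0.0182) and power of 80.6%. That test does not depend on how many eyes are at level 53 or higher.

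**2. What the vtDR count implies.** Let q be the share of vtDR eyes at ETDRS 53 or higher. The documents do not give q, so a range is assumed and eyes are treated as independent. If enrolment ended with exactly 20 vtDR eyes, the expected number at level 53 or higher would be 20q, and the chance of fewer than 20 would be 1 − q^20. The vtDR eyes needed for an expected 20 are 20/q, rounded up.

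| q | Expected eyes at 53+ | Chance of fewer than 20 | vtDR eyes for an expected 20 |
|---|---|---|---|
| 0.50 | 10 | >99.9% | 40 |
| 0.75 | 15 | 99.7% | 27 |
| 0.90 | 18 | 88% | 23 |
| 0.95 | 19 | 64% | 22 |

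Only q = 1 makes 20 vtDR eyes equivalent to 20 eyes at level 53 or higher. The chances apply to a stop at exactly 20 vtDR eyes; 20 is a minimum, so the final count may be higher.

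**3. Effect on weighted sensitivity.** Let k be the number of distinct eyes at level 53 or higher among 200 mtmDR(+) eyes. Assume sensitivity s1 = 0.82 below level 53, s2 = 0.95 at or above it, and independent eyes (optimistic, since fellow eyes are correlated).

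- Estimate = 0.8 × s1 + 0.2 × s2.
- Variance = 0.64 × s1(1 − s1)/(200 − k) + 0.04 × s2(1 − s2)/k.
- One missed severe eye moves the estimate by 20/k percentage points.
- Draws needed for a 20% share, keeping the other eyes as they are = (200 − k)/4.

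For k = 20: 0.64 × 0.1476/180 + 0.04 × 0.0475/20 = 0.000525 + 0.000095 = 0.000620, so SE = 2.5 points.
For k = 5: 0.64 × 0.1476/195 + 0.04 × 0.0475/5 = 0.000484 + 0.000380 = 0.000864, so SE = 2.9 points.

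| k | SE (points) | Shift per missed eye (points) | Draws needed | Draws per eye |
|---|---|---|---|---|
| 20 | 2.5 | 1.0 | 45 | 2.25 |
| 10 | 2.6 | 2.0 | 47.5 | 4.75 |
| 5 | 2.9 | 4.0 | 48.75 | 9.75 |
| 2 | 3.8 | 10.0 | 49.5 | 24.75 |
| 0 | not computable | – | – | – |

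**4. Sensitivity to the assumed values.** With equal sensitivity in both groups, the effective number of eyes is 1/(0.04/k + 0.64/(200 − k)). That gives 180 at k = 20, 136 at k = 10 and 89 at k = 5, a steeper loss than in step 3. The assumed severe-eye sensitivity therefore matters. I do not convert this to power, because the plan sets no test for the weighted estimate.

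**The case against.** **The intent may already be 20 eyes at level 53 or higher.** SAP Section 3.1 states that base as a minimum and applies the same gradable-and-sufficient test that Section 4 applies to vtDR eyes. The word vtDR in Section 4 may be shorthand. This is plausible and makes the fix easy, but the enrolment condition as written does not say it.

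**A reader might infer that enrolment would close with only a handful of severe eyes.** The documents do not support that. The 200 and 140 minima also apply, 20 is a minimum, the protocol expects at least 40 vtDR eyes, and no edema-only share is given. Protocol 5.4 excludes previously diagnosed macular edema as well as severe non-proliferative and proliferative disease, so the mix cannot be predicted either way.

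**A reader might infer that the trial's main conclusion is at risk.** It is not. The weighted estimate has no hypothesis, success rule or power of its own, and the protocol's primary endpoint is unweighted sensitivity and specificity only. Under the assumptions in step 3, the SE rises only from 2.5 to 2.9 points between 20 and 5 eyes.

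**A reader might infer that the weighted group should become vtDR**, because SAP Section 4 mentions vision-threatening incidence. But the Statistical Analysis text in SAP Section 5.1 gives the purpose as extrapolation to populations with more eyes at level 53 or above, and the endpoint and resampling text use level 53 throughout. Changing the group would alter an endpoint population discussed with FDA.

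**The Data Transfer Plan is not among the documents.** It holds the enrichment details and might include a level 53 count. That limits what can be said about monitoring, but not the mismatch within the SAP.

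**Conclusion.** The mismatch is real on the text. All the stated enrolment minima can be met with fewer than the 20 eyes at ETDRS 53 or higher that SAP Section 3.1 requires for the weighted endpoint. Whether that happens, and by how much, cannot be determined from the documents.

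The consequence is confined to the precision of the weighted sensitivity, PPV and NPV. For weighted sensitivity the loss is small with 10 or more such eyes and becomes material with very few (SE 3.8 points at 2 eyes, no estimate at 0). These figures assume 200 mtmDR(+) eyes, sensitivities of 82% and 95%, and independent eyes; equal sensitivities would make the loss larger. The unweighted sensitivity and specificity tests stand as planned. This should be fixed, but it is not a condition for those tests to be valid.

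**What to change.** 1. In SAP Section 4, restate the condition as: *enrolment continues until at least 20 reading-centre gradable and sufficient eyes with ETDRS level 53 or higher are confirmed.* This matches SAP Sections 2, 3.1 and 5.1. Also correct the one place in Section 4 that says greater than 53 where the rest says at least 53.
2. In Protocol 7.4, add an ETDRS 53-or-higher flag to the categories the monitoring statistician sees, and carry it into the Data Transfer Plan if it is not already there.
3. State in the SAP that if the 282-subject maximum is reached first, the weighted analysis is reported with the actual number of distinct eyes at level 53 or higher, and the 20-eye figure is restated accordingly.
4. Reconcile the vtDR definition and count: ETDRS 50-85 and at least 40 eyes in the protocol, against 53-85 and at least 20 eyes in the SAP.

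The cost is a few sentences and one data field; under Protocol 1.2 the reading centre already grades ETDRS level and macular edema for every eye. The flag carries no IDx-DR result, so masking is unaffected. The downside is that enrolment may run slightly longer, within the existing maximum.
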